## Methods

### Study Design

The proposed hybrid type 1 study is a single-site, 2-arm, single-blind RCT designed to simultaneously assess (1) feasibility and acceptability of an RCT of stepped-care web-based parent support (ie, adherence, fidelity, costs, and acceptability) and (2) efficacy of the stepped-care I-InTERACT-North program in improving positive parenting skills and child behavior among families of children with CHD.

Hypothesis 1: based on our pilot data, we hypothesize that the stepped-care program will demonstrate program feasibility (ie, adherence and fidelity, >70%) and high acceptability (ie, based on postintervention program ratings, thematic analysis of feedback, >90%) across CHD families.

Hypothesis 2: we hypothesize that positive parenting skills and child behavior will improve at the end of the treatment among participants in the treatment arm compared to CAU and remain improved compared with CAU at 12 months. We consider positive parenting skills as the primary proximal outcome and child behavior (co–primary outcome) as mediated by improvements in parenting. We also consider secondary outcome changes in parent mental health and family quality of life.

After completion of baseline measures, families will be randomized to receive CAU or active I-InTERACT-North stepped-care treatment. Randomization will be stratified by sex assigned at birth (male, female) and baseline child behavior severity (Eyberg Child Behavior Inventory [ECBI] intensity *t* score above or below cutoff of 60) and executed by a computerized randomization system on REDCap (Research Electronic Data Capture; Vanderbilt University) [30]. Families in both conditions will complete follow-up measures at 3 months, 6 months, and 12 months postbaseline (Figure 1). Families randomized to CAU will receive no direct parent treatment other than clinical care provided in cardiac follow-up (ie, child assessment and consultation), which will be documented accordingly. The CAU families will be offered I-InTERACT-North after completion of their 12-month follow-up measurements. Participants cannot be blinded to their condition, but they will be blinded to primary outcomes and hypotheses. Independent study staff responsible for coding the primary outcomes (ie, positive parenting skills) will be blind to participant allocation, outcomes, and baseline or follow-up status.

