### Primary Outcomes

Feasibility outcomes include program reach and adherence (ie, proportion of eligible families who enroll and complete the study) and program fidelity (assessed with a therapist checklist completed after every session).

Two primary outcomes are evaluated for the second objective: positive parenting skills and child behavior. Positive parenting skills are evaluated using the Dyadic Parent-Child Interaction Coding System (DPICS [34]). One member of a team of 3 coders, blind to condition, will observe a 5-minute recording of parent-child interactions and count the frequency of specific positive parenting skills (eg, labeled praise, behavioral descriptions, commands, questions, etc). In our team’s previous studies, interrater reliability coefficients were very high (>0.96 [28,29]). Throughout the RCT, 20% of all videos are double coded to prevent coder drift and coders meet regularly for consensus. In the case that reliability falls below α=.80, the team of coders will convene to reestablish consensus. The second primary outcome, child behavior, is measured with the parent-report ECBI [35]. The ECBI consists of 36 items describing various behavior concerns (eg, noncompliance, emotional regulation), each rated in terms of frequency from 1 (Never) to 7 (Always) as well as whether parents perceive it to be a problem for them (Yes/No). The ECBI yields an intensity score based on frequency of concerns and a problem score representing the number of concerns noted to be problems for the parents. Previous studies have demonstrated good convergent validity of the DPICS and the ECBI for assessing the impact of parenting skills on child behavior [34].

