### Sample Size and Power Analysis

Based on the size of the research registries available for recruitment and pilot estimates of consent rate (70%), we anticipate that 382 families will consent to participate in the RCT. Using pilot estimates of adherence rate (86%), we anticipate that 328, 282, and 244 families will complete the 3-month, 6-month, and 12-month follow-up measurements, respectively. Samples of 122 participants in each condition at 12 months postbaseline will provide >95% power to detect an effect size of 0.64, which is a medium to large effect size conservatively based on our pilot data. This sample size also achieves a power of 95% for subgroup analyses with subgroups with a split of 50%, which is consistent with or close to that of our pilot data.

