#### Primary Efficacy Analysis

Primary efficacy analysis will be conducted using an intent-to-treat approach. Generalized estimating equations for longitudinal count-level data having a Poisson distribution will be used to examine changes on the DPICS positive parenting composite. We will account for missing data with the Kenward-Roger degrees of freedom command and using a random intercept with the appropriate covariance structure to allow for unbalanced covariance matrices. The main effect of the program on positive parenting skills will be tested by linear contrast of adjusted DPICS mean change scores from baseline to 3 months between groups. We will also refit the regression model to include stratification variables (sex, baseline behavior intensity) and intervention step as moderators of the effect of treatment. The co–primary outcome of child behavior, as well as continuous secondary outcomes of quality of life and parent mental health, will be tested with repeated-measures analyses including condition, stratification variables (ie, sex assigned at birth and baseline child behavior severity), intervention step, and their interactions as fixed effects. Individual subjects as random effects will be adjusted to the data [43,44]. Sensitivity analyses will be carried out to replicate the analyses [29] from the initial adaptation of the I-InTERACT-North program into a stepped-care model for children with neurological risk, examining the preliminary efficacy in changes in positive parenting skills and child behavior based on intervention step. Finally, we will replicate the analyses conducted by Wade and colleagues [25] in the RCT of the original version of I-InTERACT for children with TBI, testing a moderated mediation model using regression-based process modeling to assess the indirect effects of treatment group on child behavior at 12-month follow-up through the change score for positive parenting.

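### The primary DPICS test contrasts arms on change from baseline without naming baseline DPICS as a covariate; unless *adjusted* already covers it, precision is lost, though no bias arises

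*Protocol article*

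**What the plan says.** All references are to the protocol article.

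- **Model** (Primary Efficacy Analysis): "Generalized estimating equations for longitudinal count-level data having a Poisson distribution will be used to examine changes on the DPICS positive parenting composite".
- **Test** (same section): the main effect "will be tested by linear contrast of adjusted DPICS mean change scores from baseline to 3 months between groups".
- **Covariates** (same section): the only ones listed for this model come in a second step: "We will also refit the regression model to include stratification variables (sex, baseline behavior intensity) and intervention step as moderators" of the treatment effect. The baseline behaviour variable there is the ECBI intensity stratum, not DPICS.
- **Timing** (Study Design): "After completion of baseline measures, families will be randomized to receive CAU or active I-InTERACT-North stepped-care treatment". Allocation is stratified on sex and ECBI intensity, not on DPICS.
- **Measurement** (Primary Outcomes): a coder "will observe a 5-minute recording of parent-child interactions and count the frequency of specific positive parenting skills". In the team's previous studies, "interrater reliability coefficients were very high (>0.96").
- **Power** (Sample Size and Power Analysis): "Samples of 122 participants in each condition at 12 months postbaseline will provide >95% power to detect an effect size of 0.64". The section also claims 95% power for subgroups with a 50% split.

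**The concern.** A baseline-to-3-month change contrast from a longitudinal count model most naturally places the baseline count among the outcomes and lets each arm have its own baseline mean. The treatment effect is then the arm difference at 3 months minus the arm difference at baseline; with a log link it is a ratio of ratios. After randomisation the second term estimates zero, so subtracting it brings in its sampling error.

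How much this costs depends on how well the baseline count predicts the 3-month count. Each count comes from one 5-minute recording, so the correlation could be modest. The figure above 0.96 does not settle this, because it describes agreement between coders, not the stability of a family's behaviour over three months. With equal variances and r below 0.5, a change contrast is less precise than comparing the arms at 3 months and ignoring baseline.

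At stake is the width of the interval for the first primary efficacy outcome, and the power left for subgroup analyses.

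**Working it through.** **Inputs from the article.** 1:1 allocation; d = 0.64; 122 per arm at 12 months; 328 families expected at 3 months, so 328/2 = 164 per arm; subgroups with a 50% split, so 122/2 = 61 per arm.

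**Assumptions.** Two-sided alpha of 0.05 (none is stated); equal SDs at both visits; 0.64 in units of the raw outcome SD; r taken over a range. Powers use the normal approximation.

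**Step 1: the plan's own figures.** For a plain two-group comparison, the standardised effect is 0.64 × √(n/2).
- n = 122: 0.64 × √61 = 5.00, power 99.9%. This agrees with the stated figure above 95%.
- n = 61: 0.64 × √30.5 = 3.53, power 94.2%. This is close to the 95% claimed for subgroups.

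**Step 2: variance under each analysis**, per family, in units of the raw variance.
- Change from baseline: 2(1 − r)
- Baseline-adjusted: 1 − r²
- Information lost by change: 1 − (1 − r²)/[2(1 − r)] = 1 − (1 + r)/2 = (1 − r)/2

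**Step 3: results.** The power columns divide the standardised effect from Step 1 by the square root of the relevant variance.

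| r | Var, change | Var, adjusted | Information lost | Power, change, 61 per arm | Power, adjusted, 61 per arm |
|---|---|---|---|---|---|
| 0.3 | 1.40 | 0.91 | 35% | 84.8% | 96.0% |
| 0.5 | 1.00 | 0.75 | 25% | 94.2% | 98.3% |
| 0.7 | 0.60 | 0.51 | 15% | 99.5% | 99.9% |
| 0.9 | 0.20 | 0.19 | 5% | >99.9% | >99.9% |

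Worked case at r = 0.3, 61 per arm: change 3.53/√1.40 = 2.99; adjusted 3.53/√0.91 = 3.71.

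**Step 4: main comparison.** With the change contrast at r = 0.3, power is 99.8% with 164 per arm and 98.8% with 122 per arm. With 164 per arm it is still 98% at r = 0.

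**Step 5: which subgroup size applies.** The article's subgroup claim rests on the 12-month sample, hence 61 per arm. The DPICS contrast is at 3 months, where a 50% subgroup would have 164/2 = 82 per arm. There the standardised effect is 0.64 × √41 = 4.10. At r = 0.3, change gives 4.10/√1.40 = 3.46, power about 93%; adjustment gives 4.10/√0.91 = 4.30, power about 99%. The shortfall is smaller at that size.

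**Step 6: does the formula carry over to counts?** A simulation of the log-link Poisson change contrast against a baseline-adjusted Poisson model used 164 per arm and overdispersed counts with mean 8 (all settings assumed). Losses were about 34%, 27–32%, 17–19% and 4–9% at observed correlations of about 0.29, 0.45, 0.62 and 0.77. These are close to (1 − r)/2, except at the highest correlation, where the loss was smaller.

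**The case against.** **The word *adjusted* may already cover this.** It is undefined, and a condensed article may leave the covariate list to the analysis plan. If it includes baseline DPICS, then in a linear model the contrast of change is identical to the baseline-adjusted comparison and nothing is lost. The sentence also fits a model in which the arms share one baseline mean. This stands: a reader might infer that the plan rejects baseline adjustment, and the text does not say so. But the article does fix a change contrast as the primary test, and the only covariates it lists enter later, as moderators. The unadjusted reading is therefore the natural one, and the sentence needs settling.

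**No single loss can be quoted.** A reader might take r of 0.3 to 0.6 as given and report a loss of 20% to 35%. The article reports no DPICS mean, variance or correlation over time, so only the range can be shown.

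**The main test is well powered either way.** This stands. Randomisation keeps the change contrast unbiased with a valid type I error, and a chance baseline imbalance is sampling variation that the standard error already reflects.

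**Poisson and change scores.** A reader might object that change scores can be negative and so cannot be Poisson. That misreads the plan: the Poisson model applies to the repeated counts, and the contrast is formed from fitted means.

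**Conclusion.** The point holds as one of precision. The article fixes the primary DPICS test as a between-arm contrast of change and names no baseline DPICS covariate. Unless *adjusted* includes baseline DPICS, a fraction (1 − r)/2 of the information is given up: 35% at r = 0.3, falling to 5% at r = 0.9, for equal variances and an assumed r. The documents support no claim of bias and no claim that the main comparison is underpowered.

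The visible consequence is for subgroups. At 61 per arm and r = 0.3, power is about 85% rather than about 96%; from about r = 0.5 upwards the change contrast does no worse than the 94.2% that the plan's own calculation yields. This further assumes that 0.64 is in raw-SD units and applies to DPICS; the article ties it to no particular outcome. Baseline adjustment is valid under randomisation and never less efficient in large samples, so this is a free improvement rather than a fatal flaw.

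**What to change.** State that the primary DPICS test is the between-arm rate ratio at 3 months from the Poisson GEE, with the post-baseline counts as outcomes and log(baseline DPICS + 1) as a covariate. Report the ratio with its confidence interval and give change scores descriptively. If *adjusted* was meant to include baseline DPICS, say so in the same sentence.

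Keeping baseline among the outcomes with a common mean across arms (visit and condition-by-visit terms, no condition main effect) is an alternative only if the working correlation is not independence. Under independence, with a separate mean for each arm at each follow-up visit, the estimating equations split by visit; the 3-month estimate is then the plain comparison of 3-month means and baseline contributes nothing.

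The cost is a sentence or two. No new data are needed, since baseline DPICS is already collected, and recruitment is expected to run to January 2028, so the change can be recorded before outcomes are analysed.

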**Methods:**

Families will be randomized (1:1) to either receive treatment or continue with care as usual for 12 months. Randomization will be stratified by child’s sex assigned at birth and baseline parent-reported child behavior intensity. Primary outcomes include positive parenting skills and child behavior at baseline, 3 months, 6 months, and 12 months. Secondary outcomes include parental mental health, quality of life, service usage, and feasibility including program reach and adherence. A sample size of 244 families will provide >95% power to detect an effect size of *d*=0.64. Based on attrition data from pilot studies, a target of 382 families will be enrolled. Parent reports of acceptability, adoption, and suggested adaptability of the program will be examined using cross-case thematic analyses. Primary efficacy analysis will be conducted using an intent-to-treat approach. Generalized estimating equations will be used to examine changes in positive parenting. Child behavior, quality of life, and parent mental health will be tested with repeated-measures analyses. Additional sensitivity and replication analyses will also be carried out.

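### The co-primary ECBI test sits in a model that already contains treatment-by-stratum interactions and intervention step, with no deciding contrast or time point, although DPICS has both

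*Protocol article*

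**What the plan says.** All of this is in the protocol article.

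- **ECBI, quality of life and parent mental health** (Primary Efficacy Analysis). These outcomes "will be tested with repeated-measures analyses including condition, stratification variables". The list continues: "ie, sex assigned at birth and baseline child behavior severity), intervention step, and their interactions as fixed effects". Subjects enter as random effects. Time is not among the listed fixed effects, and no contrast is named.
- **DPICS** (same section). The main effect "will be tested by linear contrast of adjusted DPICS mean change scores from baseline to 3 months between groups". Moderators come in a second step: "We will also refit the regression model to include stratification variables (sex, baseline behavior intensity) and intervention step as moderators".
- **Hypothesis** (Study Design). For both co-primary outcomes, "positive parenting skills and child behavior will improve at the end of the treatment among participants in the treatment arm compared to CAU", with the advantage kept at 12 months.
- **Stratification and allocation.** "Randomization will be stratified by sex assigned at birth (male, female) and baseline child behavior severity", the severity cut being an ECBI intensity t score of 60. The abstract gives 1:1 allocation.
- **Power** (Sample Size and Power Analysis). With 122 per arm at 12 months, power is above 95% for an effect size of 0.64. The section adds: "This sample size also achieves a power of 95% for subgroup analyses with subgroups with a split of 50" per cent.

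**The concern.** The two co-primary outcomes are handled differently in one paragraph. For DPICS the reader knows which comparison decides and that moderation is examined afterwards. For ECBI the moderators are already inside the testing model, and nothing says which line of output answers the efficacy question.

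Once condition-by-sex and condition-by-severity are in the model, the condition term is no longer automatically the overall treatment effect. It may be the effect in one stratum or an equally weighted average over strata, depending on coding. Intervention step complicates this further, because only treated families progress through the steps.

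At stake is whether a co-primary conclusion is fixed in advance or depends on which parameterization is reported.

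**Working it through.** **Inputs from the article:** 122 per arm at 12 months; 328 families expected at 3 months (164 per arm at 1:1); planning effect 0.64; pilot child behavior effect d=0.390 (Introduction); a subgroup split near 50%.

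**Assumptions:** alpha 0.05 two-sided (none is stated); sex split 50:50; d=0.39 used as if it were a between-arm effect; step terms left out; one normal outcome per family, standing in for the between-subject tests of the repeated-measures model.

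**1. The plan's own figures.** Power ≈ Φ(d·√(n/2) − 1.96), with n per arm.
- d=0.64, n=122: Φ(4.998 − 1.96) = 99.9%, so the claim of more than 95% holds.
- d=0.64, n=61 (half-sample subgroup): Φ(3.534 − 1.96) = 94.2%, close to the stated 95%.

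**2. Main-effects model, d=0.39.** Φ(0.39·√61 − 1.96) = Φ(3.046 − 1.96) = 86%.

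**3. Condition as an indicator-coded coefficient.** With all interactions in the model, this is the effect in the reference sex-by-severity cell.
- 50:50 severity: 122/4 = 30.5 per arm; Φ(0.39·√15.25 − 1.96) = Φ(−0.437) = 33%; simulation 31%.
- 50:50, two-way interactions only: the variance triples; Φ(3.046/√3 − 1.96) = Φ(−0.201) = 42%; simulation 42%.
- 70:30, larger stratum as reference: 42.7 per arm; Φ(1.802 − 1.96) = 44%; simulation 43%, or 49% with two-way interactions only.
- 80:20, larger stratum as reference: 48.8 per arm; Φ(1.926 − 1.96) = 49%; simulation 48%.

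The estimand moves too. Suppose the average effect is 0.64 and differs by 0.4 SD between equal-sized severity strata (assumed). The coefficient for the stratum with the smaller effect is then 0.64 − 0.20 = 0.44.

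**4. Condition as an effect-coded (type III) test.** This weights strata equally. With severity share p, the variance factor against the main-effects model is 1/[4p(1−p)].

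| Severity split | Factor | Closed form | Simulation |
|---|---|---|---|
| 50:50 | 1.00 | 86% | 85–86% |
| 70:30 | 1.19 | Φ(2.792 − 1.96) = 80% | about 78% |
| 80:20 | 1.56 | Φ(2.437 − 1.96) = 68% | 65% |

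**5. At 3 months.** With 164 per arm, the main-effects figure is Φ(0.39·√82 − 1.96) = Φ(3.532 − 1.96) = 94%. The single-cell figure (41 per arm) is Φ(1.766 − 1.96) = 42%. The gap remains at the larger sample.

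**6. If any significant treatment term were read as success** (not a rule in the article).
- Three terms (condition and its two-way interactions with sex and severity): 1 − 0.95³ = 14.3% if independent. Simulated under no effect: 13.4–13.5% with effect coding, 11.9–12.3% with indicator coding.
- Four terms (adding the three-way interaction): 1 − 0.95⁴ = 18.5%. Simulated: 16–19% with effect coding, 13.2–14.5% with indicator coding.
- A single pre-named term stays at about 5%.

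**The case against.** The hypothesis in Study Design already says what efficacy means: treatment against care as usual, at end of treatment and then at 12 months. No subgroup hypothesis is stated. A sensible analyst would report that comparison, and a journal article may leave coding and exact contrasts to an analysis plan. The working also simplifies: it has no time factor or subject effect, it uses the 12-month sample, and the pilot d is not described as between-arm.

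Much of this stands. A reader might infer that the plan carries an 18% false-positive rate. The article does not support that. The figure needs an assumed alpha, a three-way term that the article does not specify, near-independent effect-coded tests, and an any-term-counts rule that is stated nowhere and that the hypothesis argues against. A reader might also infer that one analysis suffers both the highest error rate and the one-stratum reading, but these belong to different codings. Nor does the type III test necessarily lose power: at the roughly even split the article expects, it loses none. The subgroup power sentence does not by itself make subgroup results confirmatory.

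The objection does not remove the core point. The hypothesis gives a direction and two occasions but maps to no model term. The article does not leave the ECBI model open: it states one, with the interactions inside it, next to a better-specified DPICS test.

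**Conclusion.** The concern holds in a limited form. The stated ECBI model does not isolate the overall treatment comparison that the hypothesis calls for, and it is inconsistent with how DPICS is handled. The size depends on which output is read. An indicator-coded coefficient has about 31–49% power, against 86% from a main-effects model. An effect-coded test has no loss at 50:50, about 78–80% power at 70:30 and 65–68% at 80:20. The uneven splits are a sensitivity range, since the article expects about 50%.

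These figures rest on d=0.39, 122 per arm, two-sided alpha 0.05, equal effects across strata and a simplified single-outcome model. Where severity is uneven, the coefficient figures take the larger stratum as reference. The any-term error rates (about 12–14% for three terms, 13–19% for four) are conditional on a rule that the article does not contain and are not a property of the plan. This should be corrected before outcome analysis.

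**What to change.** State that the deciding ECBI test is the single between-group contrast of change from baseline to 3 months, taken as end of treatment as for DPICS, with the 12-month contrast as the test of maintenance. Take both from a repeated-measures model with condition, time and condition-by-time, and with sex and baseline severity as main effects only. Exclude intervention step and all condition-by-stratum interactions from that model.

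Move condition-by-sex, condition-by-severity and any analysis by step to a separate refit labelled exploratory, reported as estimates with 95% confidence intervals and not used to claim efficacy. Apply the same structure to quality of life and parent mental health.

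The cost is a wording change and one extra model fit per outcome, with no new data or families. The downside is that subgroup results can no longer be presented as confirmatory. The Results section reports 24 families enrolled by September 2024 and follow-up to January 2029, so as of the article the change could be made well before analysis.

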### Intervention

I-InTERACT-North is a stepped-care web-based parenting program consisting of 3 tiered steps of increasing therapeutic intensity (Figure 2). In step 1, participants are matched with a therapist for an introductory appointment to review their concerns and goals for the program. Steps 2 and 3 combine web-based therapy sessions with web-based psychoeducational modules that introduce positive parenting skills (eg, labeled praise, reflective responses; Figure 3) as well as child behavior management strategies. Each web-based module concludes with a brief quiz to assess engagement and understanding. Parents complete the web-based modules asynchronously before their web-based therapy appointment, where they review the strategies and engage in active coaching with their therapist while their child is present. Step 2 includes the first 2 therapy sessions and step 3 consists of an additional 5 sessions. Depending on the number of steps completed, as well as scheduling of sessions, I-InTERACT-North may last anywhere from 1 day (ie, 1 single-hour session) up to 7 weeks (for weekly sessions) or 14 weeks (for biweekly sessions).

A collaborative approach to treatment planning (ie, step-up or step-down as outlined by Kennedy et al [31]) is used with families at the end of steps 1 and 2 to decide whether they will proceed with treatment. Step-up indicators include low positive parenting skills as coded from observed parent-child interactions, high child behavior severity, and high in-session ratings of the family’s “top problems” [31,32].

Each session follows a manualized therapy protocol to optimize therapist fidelity. All sessions are recorded (with written consent from the participant) and reviewed in supervision. Therapy sessions are delivered via Zoom (Zoom Video Communications, Inc) [33]. All I-InTERACT-North therapists possess masters-level (or higher) education in clinical psychology and come from diverse cultural and language backgrounds. All therapists undergo extensive training and ongoing supervision to ensure program fidelity; this includes a 2-day synchronous training course, 3-6 months of case shadowing, and regular individual and group supervision by a licensed psychologist upon commencing independent program delivery.

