### Limitations

Several limitations will be taken into consideration with respect to this clinical trial. This is a single-site study that reflects findings specific to The Hospital for Sick Children, the Toronto, Ontario, context, and a public health care system. Recruitment and intervention materials are currently available only in English, thus limiting access and generalizability to non–English-speaking families. However, several therapists are bilingual or multilingual (English and French) and interpreter services are available for recruitment, informed consent discussions, and web-based coaching sessions. Likewise, we provide families in need with tablets and web-based sticks as necessary to ensure that web-based coverage status does not pose a barrier to participation. Although the stepped-care treatment model offers increased customization and precision in our intervention approach to optimally address families’ needs, it may be challenging to elucidate differences in outcomes between those who receive exclusively an introductory appointment relative to the CAU group. It may also be difficult to control the effects of concurrent intervention services (eg, psychotherapy, rehabilitation) in evaluating the efficacy of I-InTERACT-North; however, service receipt will be explored as a secondary objective to ascertain valuable insight into additional mental health supports sought by families.

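### The by-step sensitivity analysis seeks efficacy in changes grouped by a step decided during treatment and absent from care as usual, with no valid comparator named

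*Protocol article*

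**What the plan says.** The protocol article, Primary Efficacy Analysis, states: "Sensitivity analyses will be carried out to replicate the analyses [29] from the initial adaptation of the I-InTERACT-North program into a stepped-care model". The purpose given is "examining the preliminary efficacy in changes in positive parenting skills and child behavior based on intervention step". Positive parenting (the DPICS composite) and child behavior (ECBI) are the two co-primary outcomes.

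The Intervention section describes how a family reaches a step. A collaborative planning approach "is used with families at the end of steps 1 and 2 to decide whether they will proceed with treatment". The criteria are given as: "Step-up indicators include low positive parenting skills as coded from observed parent-child interactions, high child behavior severity, and high in-session ratings". Those ratings cover each family's top problems.

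Study Design says of the control arm: "Families randomized to CAU will receive no direct parent treatment other than clinical care provided in cardiac follow-up". CAU families are offered the program only after their 12-month measures, so none has a step during the trial.

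The main efficacy test for parenting is a between-arm comparison, "tested by linear contrast of adjusted DPICS mean change scores from baseline to 3 months between groups". The Limitations section concedes that "it may be challenging to elucidate differences in outcomes between those who receive exclusively an introductory appointment relative to the CAU group". It does not mention selection into step or regression to the mean.

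**The concern.** The grouping variable arises after randomisation, exists in one arm only, and is driven by the constructs that are then analysed as outcomes. Families who go further in the program are meant to be those with lower parenting skill or more severe child behavior. If those scores were unusually poor when selection took place, they will tend to move back toward the average with no help from the program. Families stepped up because they are not improving early could show the reverse.

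The article calls this a sensitivity analysis and places it under the primary efficacy heading. A sensitivity analysis asks whether the randomised result survives other assumptions about the same treatment contrast. Change by step answers a different question and cannot do that.

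Stepped delivery is the program's defining feature, so a gain reported by step could be read as evidence that the more intensive steps work, although the trial has a randomised control arm with the same measures.

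**Working it through.** **Inputs.** The article gives no figure for the by-step analysis, so its sample-size figures set the scale.
- 382 families randomised 1:1 give 191 per arm. Retention is 86% to 3 months: 382 × 0.86 = 328.5 (the article states 328), or 191 × 0.86 ≈ 164 per arm.
- The pilot child-behavior effect is d = 0.390 (Introduction).
- Assumed, because the article gives none: no program effect; half of the treated arm stepped up (82 of 164); normally distributed scores; baseline-to-follow-up correlation r of 0.6, 0.7 or 0.8.

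**Formula.** Let the score that drives step-up have correlation k with baseline and m with follow-up. For the worse half, its mean is φ(0)/0.5 = 0.3989/0.5 = 0.798 SD. With no program effect and no time trend, the expected apparent improvement is

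0.798 × (k − m) SD.

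**Three selection rules.**

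1. *Strict selection on baseline ECBI* (k = 1, m = r): 0.798 × (1 − r).
   - r = 0.6: 0.32 SD; r = 0.7: 0.24 SD; r = 0.8: 0.16 SD.
   - Relative to the pilot effect: 0.16/0.39 = 41% to 0.32/0.39 = 82%.
2. *Partial selection on baseline* (k = 0.5 to 0.7, m = k × r): 0.798 × k × (1 − r).
   - Smallest: 0.798 × 0.5 × 0.2 = 0.08 SD. Largest: 0.798 × 0.7 × 0.4 = 0.22 SD.
3. *Selection only on a mid-treatment score equally correlated with baseline and follow-up* (k = m): 0 SD. If that score is closer to follow-up than to baseline (m > k), the sign reverses and benefit is understated.

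**How often this would look significant.** These are simulated trials with no program effect, tested at the 5% level. Simulation error is about 1 to 2 percentage points.

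| Selection into step-up | Apparent gain (SD) | Before-after test, 82 stepped-up families | Stepped-up families against all CAU |
|---|---|---|---|
| Strict on baseline | 0.16 to 0.32 | 64 to 92% | 46 to 76% |
| Partial on baseline | 0.08 to 0.22 | 21 to 63% | 15 to 47% |
| Mid-treatment score only | about 0 | 2 to 3% in the direction of improvement | about the same |

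**Why adding all of CAU does not repair it.** The whole CAU arm is unselected, so its expected change here is 0 and the difference keeps the full artefact. The CAU arm would remove a time trend common to both arms, but not the effect of selection.

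**What does repair it.** Applying the same baseline rule in both arms (worse half at baseline, 122 per arm at 12 months) gave rejection in about 5.6 to 5.8% of simulated trials, close to nominal. The within-arm test on the same data rejected in 81%, 69% and 52% at r = 0.6, 0.7 and 0.8.

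**The case against.** A reader might infer that the analysis is a before-after test inside the treated arm with CAU dropped, and that it will therefore show false benefit. The article does not support either statement. The sentence names no comparator and no test. The study it replicates is cited but its design is not described, and a fuller protocol or analysis plan may say more. The Limitations section also shows that the authors have step-versus-CAU comparisons in mind.

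The size of any bias is equally open. The step decision is made during treatment, partly from in-session ratings and jointly with the family, and the article does not say that baseline ECBI is the severity measure used. Under one plausible rule the artefact is zero, and under another it would hide benefit. The analysis is secondary, and the main parenting test compares the arms.

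All of this stands as a limit on the claim. It does not rescue the analysis. Whether step groups are examined before and after or against CAU as a whole, families are grouped by something that follows randomisation and has no CAU counterpart. This is also more than a detail left to an analysis plan: the article itself fixes the grouping variable, the outcomes, the efficacy purpose and the sensitivity label.

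**Conclusion.** The point holds in limited form. As described, the by-step analysis cannot separate program effect from selection, regression to the mean and time trends, and it is not a sensitivity analysis of the randomised result. The intent-to-treat comparison between arms does not depend on it.

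The artefact ranges from about 0 to 0.32 SD under the assumptions above, with its upper part comparable to the pilot child-behavior effect. The high false-positive rates apply only if step-up follows baseline ECBI closely. The retest correlation, the proportion stepped up and the selection rule are all assumptions, and the normal model is only illustrative for DPICS counts. The change is worth making before analysis, but it is not a threat to the trial's main conclusion.

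**What to change.** - Report change by step descriptively, alongside the summaries of families by program step already planned under Feasibility and Acceptability Analysis, without efficacy wording or p-values.
- For efficacy by level of need, estimate the treatment-versus-CAU difference across baseline ECBI intensity (already a planned moderator) and baseline DPICS composite. Table 1 shows both collected at baseline, and Study Design places baseline measures before randomisation in both arms.
- Keep the term sensitivity analysis for re-analyses of the randomised contrast.

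The cost is a change of wording and one extra moderator model on data already being collected. The downside is that these estimates are less precise than the overall contrast, and they answer by baseline need, not by step received.
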